#### Case management by FMG nurses

The first component of the intervention is the follow-up offered under the case management process, which is seen as a collaborative, dynamic and systematic approach to ensure and coordinate care and services for a defined clientele based on interdisciplinary practice. Here the nurse evaluates, plans, implements, coordinates and prioritizes options and services according to patient health needs, in close collaboration with the involved partners [40]. The intervention focuses on four main components: (1) A thorough evaluation of patient needs and resources; (2) Establishment and maintenance of a patient-centred, individualized service plan (ISP); (3) Coordination of services among partners; and (4) Self-management support for patients and families [41].

The main duties and responsibilities of nurses in case management will be to: (1) Evaluate the patient’s situation and needs and involve the family, with the patient’s consent; (2) Identify which partners of the CSSS and of the community network to involve; (3) Jointly plan patient follow-up by establishing an ISP with the partners and with the active participation of the patients and family — minimum of two ISP per patient: one to initiate the intervention and the other approximately 3 months later; (4) Negotiate the services and defend the rights and interests of the individual; (5) Coordinate care and services; (6) Monitor the ISP application; (7) Educate and support the person. The ISP formulation stage will be oriented towards a self-management support approach that will emphasize the following: the patient’s potential; setting objectives according to his or her perspective; developing problem-solving skills; and using the patient’s usual support system [42]. Home visits by the nurse may be required, when justified — as in the case of reduced mobility or if a home assessment is needed — while avoiding overlap with home support services already offered.

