The intervention will be implemented in each FMG by two nurses. Given the expertise of the nurses already working in the FMG and their established relationships with the medical teams and partners (e.g., community pharmacists), it is preferable that they implement the intervention rather than nurses hired for this project. This also promotes the sustainability of the intervention in the participating FMG. Nurses selected to conduct the intervention will receive five days of theory and practical training specific to case management and self-management support, provided by the Clinical Project Coordinator (described in following paragraph). Family doctors will be actively sought throughout the intervention to: identify participating patients, problems and intervention priorities, participate in ISP preparation meetings (in person or by having shared their perspective with the nurse prior to the meeting), and provide the medical components of ISP implementation. Partners include the CSSS professionals identified based on the needs of participants, such as psychosocial service providers (e.g. social worker) currently involved in a patient’s care, or additional professional resources specializing in CD management (nurse, nutritionist, etc.). The partners also include community organizations (e.g., home care services), patient associations and community pharmacists.

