### Measures

The variables defined within the logic model will be measured using instruments that are well known and have been validated in studies similar to the one proposed.

The proximal outcomes, evaluated at T0 (recruitment period), T1 (3 months) and T2 (6 months) for both groups (see Table 2), will be: (1) self-efficacy measured with the *Self-Efficacy for Managing Chronic Disease* scale [61]; (2) self-management practices, with the *Self-monitoring and Insight* sub-scale of the *health education impact questionnaire* (heiQ [62,63]; (3) health habits, using the questionnaire developed as part of the PRECISE study [64]; (4) patient activation, with the *Patient Activation Measure*[65]; and (5) psychological distress, with the *Psychological Distress Scale*[66].

**Table 2 T2:** Proposed study plan

	**Visit 1**	**Visit 2**^**1**^	**Visit 3**	**Visit 4**	**T3**^**2**^
	**T0**		**T1**	**T2**	
Time from the start of the intervention	−2 weeks	0	3 months	6 months	12 months
Verification of eligibility	√				
Informed consent	√				
Covariables: Socioeconomic level, social isolation, literacy, mental health and multimorbidity	√				
Proximal outcomes: Personal self-efficacy, self-management practices, lifestyles, activation and psychological distress	√		√	√	
Intermediate outcomes: Empowerment, quality of life and use of services	√			√	√

^1^ Visit 2 will mark the beginning of the intervention. This will be two weeks after randomization for the experimental group and 6 months after randomization for the control group.

^2^ For the experimental group and use of services only.

Intermediate outcomes, evaluated at T0 and T2 (see Table 2), will include: (1) empowerment, measured with the heiQ scale [62]; (2) quality of life, measured with the SF-12v2 scale [67]; and (3) the use of health services, measured using clinical data from the CSSS (with Magic Chronique software by MediaMed) for hospitalizations, emergency room visits and CSSS services (e.g., psychosocial services or specialized services related to the specific CD), and electronic data on visits with physicians and nurses in the FMG.

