### Stages of data acquisition and analysis

(1) **Cost analysis**. Cost analysis will be performed from an organizational perspective; that is, only costs related to the FMG and CSSS will be outlined. The costs of the intervention and of usual care will be identified. For the experimental group, the average nurse’s salary for the time devoted to intervention will be obtained (average cost per patient). The data on services obtained from the CSSS (emergency visits, hospitalizations, etc.) and from the FMG (excluding management of cases already included in the calculation) during the six-month follow-up will also be obtained and their monetary value will be estimated, using the average cost per patient for both groups. (2) **Measurement of effectiveness**. Data collected as part of the impact evaluation (intermediate outcomes) will be used to document the effects of the intervention on empowerment, quality of life, and use of services (emergency visits, hospitalizations, other CSSS services and FMG services). The effects will be measured in terms of the empowerment gained, quality of life gained, and, the reduction in use of services. (3) **Efficiency analysis**. Costs and effects will be compared, in order to identify whether the intervention or the usual care leads to better effectiveness at lower cost. Incremental cost-effectiveness ratios (ICER = Δ Effectiveness/Δ Costs) will be calculated. This component will address the following three questions: (1) How much does it cost to improve empowerment? (2) How much does it cost to improve quality of life? (3) How much does it cost to decrease use of CSSS or FMG services? (4) **Cost-benefit analysis**. A cost-benefit analysis will be performed if a reduction in the use of services is documented (see power calculation in “sample size and statistical power” section presented previously). The cost differential of the cost of services avoided, related to a reduction in the use of services for the number of patients surveyed (Δ benefits), will be compared to the cost differential of the intervention and the usual care (Δ costs) so as to assess whether the new intervention is cost-effective. We will calculate the gain per dollar invested in the intervention by estimating the Δ benefit/Δ cost ratio. If this ratio is greater than 1, a gain will be indicated; otherwise, a break-even point will be estimated by evaluating the minimum cost at which the intervention will become cost-effective. This analysis would also estimate the caseload for obtaining a break-even point and for identifying the profile of patients for whom the intervention was more cost-effective. (5) **Sensitivity analysis**. Since many uncertainties are generally present in the economic and effectiveness data, it will be important to complete the analysis by: (1) identifying and explaining the sources of uncertainty; and (2) performing sensitivity analyses by varying the value of specific parameters related to the sources of uncertainty, in order to assess the robustness of outcomes [77,79], and if necessary, to determine the break-even point of the intervention.

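### The FMG visit count in the use-of-services outcome does not exclude the intervention's own nurse contacts, although the plan makes that exclusion for costs

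*Protocol article*

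**What the plan says.** In the Measures section, use of health services is one of three intermediate outcomes. It is measured with CSSS (health and social services centre) data "for hospitalizations, emergency room visits and CSSS services", plus "electronic data on visits with physicians and nurses in the FMG". Nothing there sets case-management contacts aside.

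The section on case management describes who provides the intervention: "The intervention will be implemented in each FMG by two nurses". Of nurses already on the FMG staff it says "it is preferable that they implement the intervention rather than nurses hired for this project". The nurses assess needs, draw up and monitor an ISP, and educate and support the patient. The stated floor is a "minimum of two ISP per patient: one to initiate the intervention and the other approximately 3 months later". Under Study population, the experimental group receives this for six months while controls receive usual care.

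Under Stages of data acquisition and analysis, step (1) values FMG services for both groups "excluding management of cases already included in the calculation". Step (2) takes as effect the fall in "use of services (emergency visits, hospitalizations, other CSSS services and FMG services", with no such exclusion. Step (3) asks what it costs to reduce CSSS or FMG use. Step (4) makes the cost-benefit analysis conditional on a documented fall in service use, without naming the component that decides it.

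**The concern.** The intervention consists largely of FMG nurse contacts, and FMG nurse contacts are counted in the outcome. Experimental patients therefore accrue outcome events because the protocol is followed, and controls do not. Since the plan scores a decrease as benefit, fuller delivery gives a worse result on this component.

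Two results are at stake. One is the between-group comparison of FMG visits, which mixes the dose delivered with the response to it. The other is the incremental ratio for FMG use, where the same nurse contact enters once as intervention cost and again as a loss of effect. The cost-benefit condition is also exposed, because its wording would allow it to be read on total use.

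**Working it through.** The article gives no figure for service use, so there is none to reproduce. Its sample-size calculation does not bear on this point. The check sets the sections side by side and then uses labelled assumptions to show how the bias works.

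**1. Overlap and timing.**
- Counted in the outcome: FMG nurse visits (Measures).
- Delivering the intervention: FMG nurses, two per FMG (Case management by FMG nurses).
- When: the first ISP opens the intervention and the second follows about three months later, so both fall within the six months compared.
- Exclusion of case management: present for costs, step (1); absent from Measures and from effects, step (2).

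**2. FMG-visit component.** Let *c* be the recorded case-management contacts per experimental patient in six months (0 in controls), and *d* the true fall in other FMG visits relative to controls.

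Recorded difference in FMG visits = *c* − *d* (positive means more use).

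Assume each minimum ISP is logged as one visit, so *c* = 2; if the needs evaluation is a separate visit, *c* = 3. Assume 1 to 3 ordinary FMG nurse visits per six months.
- *c* = 2: 2/3 = +67% to 2/1 = +200%.
- *c* = 3: 3/3 = +100% to 3/1 = +300%.

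With an assumed true fall of *d* = 1 and *c* = 2, the recorded difference is 2 − 1 = +1. A real decrease is reported as an increase.

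**3. Ratio for FMG use.** The effect term, as a reduction, is *d* − *c* = 1 − 2 = −1 as written, and +1 once the contacts are excluded. The cost term is the same either way, because step (1) already separates case management. The sign of the ratio then depends only on whether the contacts are counted.

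**4. Only if the components were added together.** Let *b* be baseline emergency visits plus admissions per six months and *r* their relative reduction, with other use unchanged.

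Change in the sum = *c* − *b* × *r*. With *c* = 2 the sum falls only if *b* > 2/*r*:
- *r* = 30%: *b* > 2/0.30 = 6.7.
- *r* = 50%: *b* > 2/0.50 = 4.

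At *r* = 30%:

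| *b* | *c* = 2 | *c* = 4 |
|---|---|---|
| 2 | 2 − 0.6 = +1.4 | 4 − 0.6 = +3.4 |
| 3 | 2 − 0.9 = +1.1 | 4 − 0.9 = +3.1 |
| 5 | 2 − 1.5 = +0.5 | 4 − 1.5 = +2.5 |

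**5. Emergency visits and hospitalizations on their own.** The change is −*b* × *r*, and *c* does not enter. For *b* = 3 and *r* = 30% it is −0.9, however many case-management contacts are recorded.

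**The case against.** The strongest reply is that the authors saw the overlap. Step (1) removes case management, step (2) refers to FMG services straight afterwards, and the exclusion may have been meant to carry forward. Which encounters count as a visit is also the kind of operational detail that a condensed article leaves to the full protocol. This stands in part: a short clarification may be all that is needed. But the exclusion is worded as a guard against costing the same item twice, a reason that does not reach step (2). Measures, which defines the outcome, does not mention it. The article fixes the rule in one place and omits it in the two places where it governs the effect.

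It is also true that the article does not say each ISP or evaluation is logged as a visit in the FMG data. That leaves the size open. The direction does not change if any of these contacts are logged.

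A reader might infer three stronger things that the article does not support.
- *That the outcome hides any reduction in hospital use.* The components are listed one by one and never summed, and separate counts of emergency visits and hospitalizations would still show a fall.
- *That CSSS services are also the intervention itself.* They are not: "Partners include the CSSS professionals identified based on the needs of participants". If coordination leads to more partner care, that is a real change in use and belongs in the outcome.
- *That the outcome should be cut down to hospital use because the objectives name it.* The bracketed mention of emergency visits and hospitalizations in the Objectives describes the eligible patients. The outcome named there is health care use, without restriction.

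**Conclusion.** The point holds for one component. FMG visits as defined in Measures, and the economic ratio built on them, are biased towards more use under the intervention, because the exclusion made for costs is not made for effects. The bias is about one visit for each case-management contact recorded. At the two-ISP minimum that is 2 visits per experimental patient in six months, or 67% to 200% of an assumed 1 to 3 ordinary nurse visits. These percentages rest on assumed visit rates and on each ISP being logged as a visit.

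Emergency visits and hospitalizations are untouched when analysed separately. They are drawn in only if components are combined, or if the cost-benefit condition, which names no deciding component, is read on total use. Service use is one of several outcomes and none is designated primary, so the matter does not threaten the trial as a whole. It does make the FMG-use result and its ratio hard to interpret, and should be settled before the data are analysed.

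**What to change.** 1. In Measures and in step (2) of the economic section, exclude case-management encounters and ISP meetings from the FMG visit count. Identify them from the standardized checklist that nurses complete after each encounter, described under the implementation analysis. Report them separately as intervention delivered.
2. Analyse emergency visits, hospitalizations, other CSSS services and the remaining FMG visits as separate components. Keep CSSS services as an outcome.
3. In step (4), state that the condition for the cost-benefit analysis is judged on emergency visits and hospitalizations, not on a total that includes intervention contacts.

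The cost is a few sentences and a step linking checklist dates to FMG visit records, with no new patients or data collection. One limit should be acknowledged. A case-management encounter may replace an ordinary nurse visit, so the exclusion could make remaining FMG use look somewhat lower in the experimental group. Showing the excluded contacts beside the remaining visits lets the reader see both.

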#### Sample size and statistical power

When analyzing quantitative data, we must take into account that part of the effect is potentially associated with each of the eight case management nurses. The intra-nurse or intracluster correlation (ρ) is unknown, however, and is specific to each variable. On the other hand, given that series of standardization measures will be implemented to minimize nurse-specific effects, we anticipate that the intracluster correlation will not be higher than 0.10. Sample size was therefore calculated using this maximal anticipated ρ-value. Results indicated that a standardized effect size (ES) of 0.5 (qualified as medium [73]) will be detectable with two groups of 200 participants (25 per nurse) for a two-tailed test with the α level set at 0.05 and a power of 80% [74]. An ES of at least this magnitude can be expected since it was observed in a previous study [75] and in unpublished data from the CSSS de Chicoutimi. An ES of at least 0.5 also represents the clinically significant effect needed to justify the pragmatic integration of the intervention into the services already provided. For example, in the case of patient empowerment, the ability to detect an ES of 0.5 translates into the capacity to detect any difference of at least half a point within different domains of the heiQ, since the overall standard deviation is about 1 point [76]. The detection of smaller differences is irrelevant since it is not clinically significant.

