### Strengths and limitations

The study design will not allow us to determine the individual effects of each component (case management and self-management group support) of the intervention. It was conceived in order to evaluate the addition of the self-management component for some patients who can benefit from it according to primary care practitioners’ perspective. Independent applications for funding are planned in order to evaluate the effects of each component in a near future. A contamination bias could occur between the case management nurses and the nurses involved with the patient control group. Several precautions will be taken to minimize this bias. First, no nurse will monitor both experimental group and control group. Discussions between nurses caring for the groups will be kept to a minimum with respect to the intervention and the new follow-up methods developed during the first six months of implementation. The implementation analysis will shed a qualitative light on this phenomenon. The presence of eight case management nurses raises the possibility of a “cluster” effect at the analysis level, which will be verified. However, this should be minimal since many precautions will be taken to reduce it: proper training of eight case management nurses to ensure standardization; the important role of the Clinical Project Coordinator in maintaining a comparable level of intervention among the eight nurses; regular discussions (every 1.5 months) among case management nurses. Repeat surveys induce a learning effect; however, the time-lapse between each survey questionnaire will be sufficient for the effect to be minimal. Regarding external validity, the pragmatic nature of the effects evaluation favours generalization. Analysis of the implementation process will identify the factors to be considered and the conditions to be put into place to support implementation of the intervention in other Quebec FMG.

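### The stated 80% power for an effect size of 0.5 does not follow from its inputs, and the clustering it implies is not that of the trial described; the trial is not shown to be underpowered

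*Protocol article*

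**What the plan says.** All the inputs are in the protocol article, section Sample size and statistical power.

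- **Source of clustering.** The section says that "part of the effect is potentially associated with each of the eight case management nurses".
- **Intracluster correlation.** The authors write that "we anticipate that the intracluster correlation will not be higher than 0.10", and then that "Sample size was therefore calculated using this maximal anticipated ρ-value".
- **Sample and effect.** The result is that "a standardized effect size (ES) of 0.5 (qualified as medium [73]) will be detectable with two groups of 200 participants (25 per nurse").
- **Test.** The statement is made "for a two-tailed test with the α level set at 0.05 and a power of 80" per cent.

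Two other sections describe who is treated by whom. Study population gives 50 experimental patients in each of four practices (200 in all). It keeps the 200 controls on usual care for six months before they are offered the same intervention. Strengths and limitations lists the precautions against contamination: "First, no nurse will monitor both experimental group and control group".

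The article does not say whether the correlation was applied to one group or both, how many nurses care for the controls, or which formula and degrees of freedom were used. The method is given only by citation.

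**The concern.** The sentence reads as a standard two-group clustered calculation, with 200 per group in clusters of 25 and a correlation of 0.10. Those inputs can be put straight into the usual design-effect formula, and 80% does not come out.

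The second difficulty is structural. The section attributes clustering to eight nurses, and eight caseloads of 25 fill only one group. A formula that clusters both groups needs a second set of caseloads of 25 among the controls, which the article does not describe.

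This is the article's only power statement. It is offered for the effects evaluation as a whole, and the Economic analysis refers back to it where it makes the cost-benefit analysis conditional on a documented reduction in service use. The section also makes 0.5 the threshold of clinical relevance and dismisses smaller differences, so power at 0.5 is the figure a reader will use to interpret a null result. The Data analysis plan turns to multi-level analysis if a nurse effect is found, so the number of nurses and the group they belong to will matter for inference.

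**Working it through.** **Inputs** (Sample size and statistical power unless noted): n = 200 per group; m = 25 per nurse; ρ = 0.10; effect size 0.5 SD; two-sided α = 0.05 (z = 1.96); power 80% (z = 0.8416); eight case management nurses. From Study population: controls on usual care for the six months compared. From Strengths and limitations: no nurse shared between groups.

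**Step 1. Try to reproduce the 80%, with both groups clustered.**

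- Design effect = 1 + (m − 1)ρ = 1 + 24 × 0.10 = 3.4.
- Effective size = 200 / 3.4 = 58.8 per group.
- Unclustered requirement = 2 × (1.96 + 0.8416)² / 0.5² = 62.8 per group. Multiplied by 3.4 this is 213.5, or 214 per group against 200.
- Standard error = √(2 × 3.4 / 200) = 0.1844, and 0.5 / 0.1844 = 2.71.
- Normal-theory power = Φ(2.71 − 1.96) = **77.4%**.
- Effect size detectable with 80% power = 2.8016 × 0.1844 = **0.517**.

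Other two-sided versions of the same structure do not recover 80%:

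| Version, both groups clustered | Power |
|---|---|
| Normal | 77.4% |
| t on 398 df | 77.2% |
| t on effective sample size | 76.7% |
| Design effect taken as 1 + mρ | 76.2% |
| t on 14 df (eight nurses in each group) | 71.3% |

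The last row corresponds to a detectable effect size of 0.556. It supposes 16 nurses, which the article does not state. Ignoring clustering altogether gives 99.9%, so that is not the source of the 80% either.

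**Step 2. Compare the structure with the trial.**

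8 nurses × 25 patients = 200, which is the experimental group alone. Controls are not treated by these nurses during the comparison. They may see other nurses, but the article gives neither the number nor the caseload of those nurses, so a cluster size of 25 for controls has no stated basis.

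**Step 3. Recalculate with clustering in the experimental group only.** This assumes equal total variance in the two groups and independent controls.

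- Variance of the difference = 3.4/200 + 1/200 = 0.017 + 0.005 = 0.022; standard error = 0.1483; 0.5 / 0.1483 = 3.37.
- Satterthwaite df = 0.022² / (0.017²/7 + 0.005²/199) = 11.7.

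| Reference distribution | Power at 0.5 | Detectable effect size at 80% |
|---|---|---|
| Normal | 92.1% | 0.42 |
| t, Satterthwaite 11.7 df | 86.9% | 0.45 |
| t on 7 df | 82.3% | 0.48 |

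All figures are before any loss to follow-up and without baseline adjustment.

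**The case against.** The strongest defence is rounding. The article gives the effect size to one decimal and says that 0.5 is detectable. The normal-theory value of 0.517 rounds to 0.5, and the gap at exactly 0.5 is 80 − 77.4 = 2.6 points, or 14 patients per group. This may well be how the sentence arose, and it makes the discrepancy small. It does not make 80% the power at 0.5, which the same paragraph treats as the clinical threshold.

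Other routes do reach 80%. The correlation is a maximum, and with both groups clustered the normal formula gives 80% at ρ = 0.091. Baseline adjustment is planned for the 3-month outcomes; an assumed baseline correlation of 0.3 gives 81.1% by normal theory. These points stand as reasons not to claim that 80% is unattainable. They do not rescue the statement, because the article says that 0.10 was the value used and states no baseline correlation.

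It is also fair that choosing a t reference over a normal one is a matter of method, and that the cited method cannot be inspected here. For that reason 77.4% is the main two-group figure. The 71.3% is conditional on eight nurses in each group.

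Finally, the defence can say that the described design supports at least 80% before loss. That is correct, and it limits the point to a misstated calculation.

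**Conclusion.** The point holds as a correction to the power statement. Taken as written, with clustering in both groups, the inputs give 77.4% power by normal theory, or a detectable effect size of 0.52, against a stated 80% at 0.5. The calculation also uses or implies a structure that the trial does not have, since the eight nurses' caseloads make up the experimental group only. On the described structure, power is about 82% to 92%, with 86.9% by Satterthwaite.

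A reader might infer from the 77% or the 71% that the trial is underpowered. The documents do not support that. Both figures belong to a structure in which controls are also clustered in nurses with 25 patients each, and the 71% further needs 16 nurses. A reader might equally infer that no reading can yield 80%; the alternatives above show that this is too strong.

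The result rests on ρ = 0.10 as stated, equal total variances, no loss to follow-up, no baseline adjustment and, for the one-group calculation, controls treated as independent. If controls share usual-care nurses to a material degree, power would fall below the one-group figures by an amount that the article does not allow one to calculate.

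**What to change.** Rewrite the sample size paragraph so that it agrees with Study population and Strengths and limitations:

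- State that the experimental group is nested in eight nurses with 25 patients each and that controls are not nested in those nurses during the six months compared.
- Give the formula and the degrees of freedom, and report the resulting power at 0.5 and the effect size detectable with 80% power. At ρ = 0.10 these are, for example, 86.9% and 0.45 with Satterthwaite degrees of freedom.
- If the two-group clustered formula is kept, say why it applies to controls, and state about 77% power at 0.5 or a detectable effect size of about 0.52.

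The cost is one reworded paragraph. It needs no extra patients and no change to the design or the analysis.
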